## **Investigational product, dosage and administration**

### **Basic Medication:**

#### **First-line medication: Metformin, orally taken**

- 1.5g per day (adjust the dose between 1-1.7g per day according to subject's specific situation).
- Investigators will provide guidance towards the brand, form, dosage and frequency.

#### **Second-line medication: Insulin, subcutaneous injection**

- Daily dose individualized.
- Investigators will provide guidance towards the brand, type, dosage and frequency.
- Insulin initiation suggestions: from the screening periods, if the subject's  $HbA1c \geq 7\%$ , the researchers can decide whether to initiate insulin therapy (metformin is used in the meantime) for the prompt control of blood glucose ( $HbA1c \leq 7\%$ ).
- Insulin adjustment recommendations:
  - Investigators can adjust the insulin dosages, change the insulin forms and stop the injections based on their own clinical experience, according to the subject's blood glucose, physical conditions and other indicators.
  - First reach the general blood glucose control level, then the ideal level, until the target level or the best appropriate level according to investigators.
  - To avoid hypoglycemia first, then control hyperglycemia.

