### Study design

This is a multi-center, open-label, 1:1:1 randomized controlled trial, compromised of a 6-week run-in period and the 104-week treatment period.

---

Target population: LADA patients signed an informed consent ( the definition of LADA subjects please refer to the inclusion standards of the study) ; aged 18-70 years old; duration should be less than 4 years.

Randomize all subjects who meet all eligibility criteria and do not meet any of the exclusion criteria into three groups by a central dynamic random method: metformin (and insulin) , metformin (and insulin) + saxagliptin , metformin (and insulin) + saxagliptin + vitamin D3.

The main purpose of this study: evaluate whether saxagliptin (and vitamin D3) as add-on therapy to metformin (and insulin) can better protect islet beta cell function than metformin (and insulin).

Safety objective: Adverse events, serious adverse events, blood glucose, blood routine, serum creatinine, serum calcium and 25 (OH) D monitoring.

---

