Insulin has been widely used in clinic for nearly 100 years. Its remarkable glucose lowering effect has been approved in numerous patients. Evidence-based strategies for preservation of  $\beta$  cell function in LADA are rare, but insulin therapy had been shown to have a beneficial effect in pilot studies . Thus, this study will use insulin as a second-line basic medication. Insulin will be added to treatment when target glucose level cannot be reached, or clinicians find it difficult to control the glucose by metformin alone. To meet the individualized needs for daily life and work according to patients conditions, researchers could choose the most suitable insulin type, dosage and injection frequency for each subject, in order to lower the incidence of hypoglycaemia and maintain an ideal glucose level safely.

DPP-IV, as a widely expressed enzyme, plays an important role in the development, activation and immune regulation of T cells. A randomized double-blind placebo-controlled parallel trial in the UK showed that when saxagliptin 5 mg/day or placebo were added to insulin or insulin plus metformin treated patients with T2DM for 52 weeks, the saxagliptin group had more stable and long-lasting glucose-lowering effect, and the patients were better tolerated . Our previous randomized-controlled pilot study showed that DPP-4 inhibitors could significantly improve islet  $\beta$ -cell function in patients with LADA . Clinical studies have demonstrated that either saxagliptin (5mg/d) alone or in combination with other drugs can reduce the patient's HbA1c and improve the function of pancreatic  $\beta$  cells. In this study we will use saxagliptin (5mg/d) plus metformin (and insulin) to treat LADA patients, and expect to see the better  $\beta$  cell protective function.

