## **4.3 Method of Randomization**

A central randomization system will be adopted, and the study population will be stratified based on the following: fasting C-peptide (FCP)  $\geq 300$  pmol/L and  $< 300$  pmol/L; GADA titer  $\geq 0.3$  and  $< 0.3$  index; BMI  $\geq 25$  kg/m^2 and  $< 25$  kg/m^2. Patients will be randomized 1:1:1 into the following three intervention groups: metformin (and insulin), metformin (and insulin) plus saxagliptin, metformin (and insulin) plus saxagliptin and vitamin D3.

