#### Second-line drug: Insulin, injected subcutaneously

- Daily dosage personalized

- The brand, dosage form, primary dosage, and frequency of insulin are decided by the investigator
- Advice towards the initiation of insulin: from the beginning of the screening stage, if the subject has a level of HbA1c  $\geq 7\%$ , the investigator can decide whether or not to initiate insulin treatment (on the basis of continuing metformin), in order to better control the patient's blood glucose level ( $\text{HbA1c} \leq 7\%$ )
- General advice towards the adjustment of insulin dosage:
  - The investigator should adjust the dosage and dosage form and decide whether or not to cease the use of insulin according to the patient's blood glucose level, physical condition, and the investigator's clinical experience;
  - First achieve the glycemic control at an average level and then adjust towards the ideal level, until the patient's blood glucose has reached standard or until the investigator thinks the patient's glucose level is best controlled
  - First avoid hypoglycemia and then control hyperglycemia.

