## **6.4 Visiting time**

### **Screening**

#### **6.4.1 Visit 1 (Week -6 - Week 0) 【outpatient visit】**

- Sign written informed consent.
- Medical history
- Physical examination
- Distribution of patient diary and glucose meter
- Initiation or adjustment of basic medication
- Record of past/ concomitant medication (record medication used within 6 months before the screening date)
- MMTT test 0, 60, 120 min blood glucose (conduct at each study site); 0, 60, 120 min C-peptide (deliver to the central laboratory)
- GADA, 25(OH)D test, gene analysis (deliver to the central laboratory)
- HbA1C, blood routine test, blood biochemical, blood electrolyte, urine pregnancy test, 24-hour urine calcium and phosphate
- 12-ECG
- BUS of urinary system
- Tests for complications

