### **7.1 Efficacy assessments**

- C-peptide: they were tested in a central laboratory. Detection was carried out by chemiluminescence using a commercially available kit (Adiva Centaur System, Siemens, Germany). The intra- and inter-assay variation coefficients were 3.7-4.1% and 1.0-3.3% respectively. Fasting serum C-peptide, peak C-peptide (60 minutes) and the area under curve of the 120-minute C-peptide were measured using a mixed meal tolerance test (MMTT, as follows). Detection is performed at V1, V8, V14, V20, and V26.
- HbA1c: it was tested in local medical center laboratories independently. The measurements are performed at V1, V5, V8, V14, V20, and V26.
- MMTT: participants will be provided with instant noodles with the net weight of 75g, and without any condiment oil. Timing of the 1-hour and 2-hour postprandial tests starts from the beginning of the meal. Participants will be required to finish the meal in 15 minutes once started. Three days before the MMTT, the participants must be reminded to assure at least 150 grams of carbohydrate intake every day. Before visiting, the participants must have fasted for at least 8 hours and abstained from tobacco, alcohol and caffeine for at least 24 hours. Confirm that the patient did not take saxagliptin 3 days before visit, and did not take the insulin injection in the morning of the visit date.

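### Insulin use at randomisation, which the protocol treats as possibly protective of beta cells, is neither an allocation factor nor a stated model term, and the only pre-randomisation C-peptide precedes the run-in

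*Protocol*

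**What the plan says.** The synopsis describes a "6-week run-in period and the 104-week treatment period". Table 1 puts Visit 1 at week -6 and randomisation (Visit 2) at week 0.

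- **Insulin in the run-in.** From screening, if HbA1c is at least 7%, the decision is the investigator's. The synopsis says "the researchers can decide whether to initiate insulin therapy (metformin is used in the meantime") and section 5.2 says "the investigator can decide whether or not to initiate insulin treatment (on the basis of continuing metformin"). Visit 1 (section 6.4.1) lists "Initiation or adjustment of basic medication", with basic medication defined as metformin (and insulin). Visit 2 (section 6.4.2) allows a further adjustment.
- **Sampling.** For C-peptide, section 7.1 says "Detection is performed at V1, V8, V14, V20, and V26". HbA1c is measured at V1, V5, V8, V14, V20 and V26. Visit 2 lists neither.
- **View of insulin.** In a sentence about preserving beta-cell function in LADA, section 1.3 says "insulin therapy had been shown to have a beneficial effect in pilot studies".
- **Allocation.** Section 4.3 says "the study population will be stratified based on the following: fasting C-peptide (FCP"), and then names GADA titre and BMI. Insulin is not among the factors. The synopsis calls the method central and dynamic.
- **Model.** The synopsis model has treatment and baseline value. Section 9.4.1 specifies an MMRM, and names age, gender and physiologic status as covariates to be examined.
- **Decision rule.** Besides the between-group test, section 9.4.1 ties a declared success to an absolute change in fasting C-peptide of 100 pmol/L or less in Group B over 104 weeks.

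**The concern.** Two features of the design meet here. First, the baseline is drawn about six weeks before the first study dose, at the visit where background treatment may be started or changed. The change to week 104 therefore covers about 110 weeks and includes any response to new metformin or insulin before study treatment. No C-peptide or HbA1c is scheduled at week 0, so a statistical analysis plan could not move the baseline to randomisation.

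Second, investigators choose the insulin background, the protocol regards it as possibly protective, and it is known at Visit 2. A dynamic allocation scheme balances only the factors it is given. If arms differ by chance in insulin use, a reader will ask how much of a saxagliptin difference is insulin, and the stated model does not answer.

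At stake are precision, the credibility of the comparison, and the meaning of the within-group figures.

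**Working it through.** **1. The protocol's own sample size (section 9.2).** Inputs are means 149.2 and 108.4, SDs 84.5 and 52.8, two-sided alpha 0.025 and power 90%.

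- Difference = 149.2 - 108.4 = 40.8 pmol/L (the unit is inferred from the C-peptide thresholds elsewhere).
- Pooled SD = sqrt((84.5² + 52.8²)/2) = 70.46.
- n = 2[(2.241 + 1.282) × 70.46/40.8]² + 2.241²/4 = 74.02 + 1.26 = 75.28, rounded up to 76.
- 76/0.8 = 95, set at 100 per group.

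The figure reproduces. The point does not dispute it.

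**2. Chance imbalance in insulin use.** The documents do not give the share on insulin at Visit 2, so I assume 20%, 30% or 50%, with simple allocation and 100 per arm. The SD of the difference between two arms is sqrt(2p(1-p)/100). The exact probability comes from two independent binomials.

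| Share on insulin (assumed) | SD of difference (points) | 95% range (points) | Exact P(difference > 10 points) |
|---|---|---|---|
| 20% | 5.7 | ±11.1 | 6.3% |
| 30% | 6.5 | ±12.7 | 10.5% |
| 50% | 7.1 | ±13.9 | 13.7% |

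The normal approximation without continuity correction gives 7.7%, 12.3% and 15.7%, which is somewhat too high.

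**3. What that imbalance does to the contrast.** The shift is the imbalance times insulin's effect on the 104-week change. The documents give no such effect, so 20, 40.8 and 80 pmol/L are assumed. The 95% chance shift is 1.96 × SD × effect.

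| Insulin effect (assumed) | 20% on insulin | 30% | 50% |
|---|---|---|---|
| 20 pmol/L | 2.2 | 2.5 | 2.8 |
| 40.8 pmol/L | 4.5 | 5.2 | 5.7 |
| 80 pmol/L | 8.9 | 10.2 | 11.1 |

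The planned difference is 40.8. Even an insulin effect as large as the planned drug effect moves the contrast by under 6 pmol/L.

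**4. Where run-in change cancels and where it does not.** Let R be the mean change from Visit 1 to Visit 2, and T the mean change from Visit 2 to week 104. The change from baseline is R + T.

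- Between arms: (R + T₁) - (R + T₀) = T₁ - T₀. R precedes allocation, so its expectation is the same in every arm and it drops out.
- Within an arm: R + T. Nothing removes R.
- Group B criterion: R + T is compared with 100 pmol/L, so movement before any study drug could decide whether it is met.

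**The case against.** The strongest reply is that everything here happens before randomisation. All arms share it in expectation, the primary hypotheses are between-group, and the contrast stays unbiased with its type I error intact. That stands. A reader might infer that the early baseline biases the saxagliptin comparison; it does not.

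A reader might also infer a loss of power. If the run-in change had an SD of 20, 40 or 60 pmol/L and were independent of later change, variance would rise by 8%, 32% or 73%, and power at 80 per arm would fall from 91.8% to 89.5%, 82.1% or 70.0%. The documents support neither input. They give no SD for the run-in change, and part of it may reverse later. A correlation of -r/(2 × 70.46), about -0.28 at r = 40 and -0.43 at r = 60, removes the loss entirely. The planning SD may also already include variation from starting treatment. These figures are not evidence of an underpowered trial.

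Nor does the protocol say that the run-in must supply a post-run-in baseline. The synopsis only names the period, and Table 1 calls Visit 1 screening. The run-in cannot be said to fail a stated purpose.

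Finally, an unstratified prognostic factor is ordinary, fasting C-peptide is stratified and may be related to insulin need, and further covariates and the insulin-dose baseline can be left to the statistical analysis plan. This limits the size of the point. It does not answer it for the allocation factors, which the protocol fixes and which cannot be changed once patients are randomised.

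**Conclusion.** The concern holds as a matter of precision and interpretability. Insulin status at randomisation is recorded, discretionary and regarded by the protocol as possibly protective, yet it is left out of both the allocation and the stated model. Under simple allocation at 100 per arm, with 30 to 50% assumed on insulin, the chance of a gap above 10 points between two arms is about 10 to 14%. The resulting shift in the contrast is about 2.5 to 11 pmol/L at its 95% limit for assumed insulin effects of 20 to 80 pmol/L. Actual imbalance under dynamic allocation may be somewhat smaller if the three existing factors are related to insulin use.

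The early baseline matters separately for the within-group changes and for the Group B criterion of 100 pmol/L, where the run-in change remains in the figure. Its size there cannot be derived from the documents.

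**What to change.** **Main change.** Record insulin use (yes/no) on arrival at Visit 2, before any Visit 2 adjustment and before the allocation is known. Add it as a fourth factor in the central dynamic randomisation and as a covariate in the primary MMRM. Visit 2 already records medication and collects the patient diary, so the cost is one more factor in the system and one more model term.

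**Optional.** Draw a fasting serum sample for C-peptide at Visit 2, before the first study dose and under the section 7.1 pre-test conditions. Use it as a second baseline covariate or in a sensitivity analysis, including one of the Group B criterion. Keep Visit 1 for eligibility, strata and the MMTT endpoints, so that fasting and stimulated C-peptide still share a baseline. The cost is one serum tube and one central assay per subject, plus fasting preparation at an existing outpatient visit. HbA1c at Visit 2 would need its own local sample.

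Neither change touches when or how insulin is given.

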## **Investigational Medication:**

Saxagliptin: 5mg per pill, orally taken, 1 pill per time, 1 time per day, take after randomization.

Vitamin D3: 400IU per capsule, orally taken, 5 capsules per time, once a day, take after randomization.

---

## **Statistical methods**

All data are entered into SAS 9.3 software (SAS Institute Inc., Cary, NC, USA). The measurements will be calculated mean, standard deviation, median, quartile, minimum, and maximum. Categorical variables will describe as frequency and percentage. Changes from baseline in primary and secondary endpoints will be analyzed using a covariance pattern model, with treatment as classification variables and baseline value as a covariate. Point estimates and 95% confidence intervals (CIs) for the mean change within each treatment group, as well as for the differences in mean change between the two groups will be estimated. Differences in categorical variables will be analyzed using Pearson  $\chi^2$ , CMH  $\chi^2$  or Fisher probabilities. For primary outcomes,  $p < 0.025$  will be considered as significant. Other outcomes  $p < 0.05$  will be considered as significantly.

Adverse events (AEs) will be summarized. The incidence of adverse events will be summarized by body system organ class and preferred term. Analyses for safety and tolerability endpoints will be summarized using descriptive statistics for continuous variables or frequency counts and percentages for categorical variables. All conclusions will be based on final analysis rather than the interim analysis.

---

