### **9.4.1 Analysis of the primary variable(s)**

The primary endpoints in the study are absolute fasting C-peptide changes between saxagliptin + metformin (and insulin) group vs. metformin (and insulin) group, and vitamin D + saxagliptin + metformin (and insulin) group vs. metformin (and insulin) group from baseline after 104 weeks of treatment. The primary endpoint will be analyzed utilizing mixed model repeated measures (MMRM) on full analysis set (FAS). Within the framework of MMRM, point estimations and 2-sided 95% CIs will be presented at each visit for the mean change within each treatment group as well as the difference of the mean change between treatment groups. The following hypothesis will be tested to establish superiority:

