### **Hypothesis Testing in Superiority Trial:**

Superiority trials are designed to show a treatment effect between saxagliptin (combined with vitamin D3) + metformin (and insulin) group and metformin (and insulin) alone group. Treatment with saxagliptin (combined with vitamin D3) + metformin (and insulin) is supposed to be superior. This superiority trial can be expressed by two hypotheses:

- Null hypothesis  $H_0: \mu_S - \mu_I = 0$ , which states that there is no difference between saxagliptin (and vitamin D3) + metformin (and insulin) group and metformin (and insulin) alone group in terms of outcome variables;
- Alternate hypothesis  $H_a: \mu_S - \mu_I \neq 0$ , which states that there is a difference.

The type I error rate for each hypothesis test is adjusted to be 0.025 considering saxagliptin + metformin (and insulin) group vs. metformin (and insulin) group and saxagliptin + vitamin D3 + metformin (and insulin) group vs. metformin (and insulin) group involved.

To determine whether saxagliptin was effective, the confidence intervals for the two groups should be constructed. If the two-tailed upper limitation of 97.5% CI is less than 0, then null hypothesis  $H_0$  is rejected and a “win” declared if the absolute change of fasting C-peptide is 100 pmol/L or less in Group B in the 104 weeks. A sensitivity analysis will also be performed on the primary endpoint with last observation carried forward (LOCF) for missing values by analysis of covariance (ANCOVA). The effect of “drop-outs” (subject withdrawals), covariates (age, gender, physiologic status), and protocol violations will be analyzed by statistical models.

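### The protocol's stated model terms omit GADA titre and BMI, two of the three factors used to balance allocation; if they are prognostic, the primary test is conservative and a little power is lost

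*Protocol*

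**What the plan says.** **Allocation.** The synopsis (Study design) says that eligible subjects are randomised "into three groups by a central dynamic random method". Sections 3 and 4.3 name the balancing factors. Section 4.3 states that "the study population will be stratified based on the following: fasting C-peptide (FCP"), cut at 300 pmol/L, and then adds GADA titre cut at 0.3 index and BMI cut at 25 kg/m². The ratio is 1:1:1.

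**Model.** The synopsis (Statistical methods) says: "Changes from baseline in primary and secondary endpoints will be analyzed using a covariance pattern model". The terms that it gives for this model are two: "with treatment as classification variables and baseline value as a covariate". No other part of the protocol lists model terms. Section 9.4.1 says "The primary endpoint will be analyzed utilizing mixed model repeated measures (MMRM) on full analysis set (FAS") and gives none. The hypothesis-testing text under 9.4.1 does mention covariates: "covariates (age, gender, physiologic status), and protocol violations will be analyzed by statistical models". That sentence also deals with drop-outs, names neither GADA nor BMI, and does not place its covariates in the primary model.

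**The concern.** An analysis should normally include the factors used to balance the arms. Balancing on a prognostic factor removes that factor's chance imbalance from the treatment contrast, so the contrast varies less from trial to trial. A model without the factor still counts its variation as residual error. The reported standard error then exceeds the true one, the confidence interval is wider than it should be, and the test rejects less often than its nominal level.

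For the primary endpoint, continuous baseline fasting C-peptide takes care of the C-peptide factor, which leaves GADA and BMI. Both are known for every randomised subject because the allocation needs them. At stake is precision that the design has already paid for. The mismatch does not bias the treatment contrast.

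**Working it through.** **Inputs (protocol section 9.2).** Mean changes 149.2 and 108.4, so δ = 40.8. SDs 84.5 and 52.8. Two-sided α = 0.025 per comparison, power 90%, drop-out about 20%.

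**The plan's own figure.**
- σ = √((84.5² + 52.8²)/2) = 70.46; z_α = 2.2414; z_β = 1.2816.
- n = 2[(2.2414 + 1.2816)/(40.8/70.46)]² + 2.2414²/4 = 74.02 + 1.26 = 75.28, so 76.
- 76/0.8 = 95, set to 100 per group. The stated figures reproduce.

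**Effect of omitting the two factors.** Let R² be the share of residual variance, after baseline C-peptide, that the GADA and BMI strata explain. The documents give no value, so 0 to 0.15 is assumed. With close balance on the strata:
- True variance of the contrast is σ²(1 − R²)·2/n, while the model without the strata reports σ²·2/n. The SE ratio is 1/√(1 − R²).
- Actual type I error of the unadjusted test = 2[1 − Φ(2.2414/√(1 − R²))].
- Unadjusted power = Φ(1.2816/√(1 − R²)).
- Adjusted power = Φ(3.5230/√(1 − R²) − 2.2414), where 3.5230 = 2.2414 + 1.2816.

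| R² | SE too large by | Actual type I error | Power, unadjusted | Power, adjusted | Gain (points) |
|---|---|---|---|---|---|
| 0 | 0 | 0.025 | 90.0% | 90.0% | 0 |
| 0.05 | 2.6% | 0.021 | 90.6% | 91.5% | 0.9 |
| 0.10 | 5.4% | 0.018 | 91.2% | 93.0% | 1.8 |
| 0.15 | 8.5% | 0.015 | 91.8% | 94.3% | 2.5 |

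The table is anchored at the 90% that the plan assigns to 76 evaluable subjects per group. Direct evaluation at 76 gives 90.8% before adjustment, because the plan's formula adds a small correction and rounds up. At 80 evaluable per group (100 less 20%) unadjusted power at R² = 0 is 92.2%. Unadjusted against adjusted power is then 92.8% and 93.5%, 93.3% and 94.7%, and 93.8% and 95.8% for R² = 0.05, 0.10 and 0.15. These gains are about 0.8, 1.4 and 2.0 points.

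**Simulation check.** Three-arm minimisation was simulated on three binary factors, with probability 0.8 of assigning the best arm, about 80 per arm and 600 runs per setting. The analysis was a single-time-point linear model, and the minimisation settings are assumptions.
- Null, R² = 0.10: mean reported SE 11.11 against an empirical SD of 10.53 without the strata; 10.55 against 10.50 with them.
- Null, R² = 0.20: 11.13 against 9.97 without; 9.97 against 9.90 with. Rejection was 1.2% without and 2.0% with, nominal 2.5%.
- With the planned effect: power 92.2% without and 93.3% with at R² = 0.10; 92.0% and 95.5% at R² = 0.20.

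These runs support the direction only. An empirical SD near 10 from 600 runs has a Monte Carlo error of about 10/√1200 = 0.29. In the run with an effect at R² = 0.20 the empirical SDs were 10.60 and 10.59, above the null-run values. The sizes in the table come from the formulas.

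**The case against.** Four points can fairly be made against this.

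1. **The synopsis line may not be a full term list.** It is one sentence covering primary and secondary endpoints together, and it omits visit and treatment-by-visit although 9.4.1 promises estimates at each visit. Section 9.1 promises a comprehensive SAP before database lock, and covariate lists are usual SAP content. This stands in part: one cannot say that the protocol forbids other terms. But it does state a covariate set, and that set leaves out two of its own allocation factors. An SAP that follows it carries the mismatch forward.

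2. **The effect is conditional.** Nothing in the documents shows that GADA or BMI predicts C-peptide change once baseline C-peptide is in the model. At R² = 0 nothing is lost. The rules of the dynamic method are not given, and drop-out of about 20% can loosen balance among those analysed, which shrinks the miscalibration. This stands in full.

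3. **The power comparison must use the right baseline.** A reader might set adjusted power against 90% and infer gains of 1.5, 3.0 and 4.3 points. That is too much, because balanced allocation also raises the unadjusted test's power, to 90.6%, 91.2% and 91.8%.

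4. **No error rate is threatened.** A reader might infer that the omission invalidates the primary test or leaves the trial underpowered. The documents support neither. The test errs on the conservative side, and the sample size rests on an unadjusted two-sample comparison, so the 90% target is still met.

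**Conclusion.** The point holds as a modest improvement in efficiency and calibration. Allocation uses three factors, and the stated model carries only the one that baseline fasting C-peptide represents. If the GADA and BMI strata explain 5% to 15% of the remaining variance, the reported standard error is 2.6% to 8.5% too large. The per-test type I error is then 0.021 to 0.015 instead of 0.025, and adjusting gains about 0.9 to 2.5 points of power at the design point. If they explain nothing, there is no loss. The sizes rest on the assumed R² and on close balance among analysed subjects. The direction, given some prognostic value, does not depend on a particular R². False-positive risk is not raised and no conclusion is put at risk.

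**What to change.** In the synopsis (Statistical methods) and in section 9.4.1, state that the primary MMRM includes GADA stratum (≥0.3/<0.3 index) and BMI stratum (≥25/<25 kg/m²), as randomised, beside continuous baseline fasting C-peptide. List treatment, visit and treatment-by-visit in the same sentence, so that it reads as the full model.

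Use the allocation factors in the secondary change-from-baseline models too. For an endpoint such as HbA1c, the endpoint's own baseline does not stand in for the C-peptide factor, so all three factors belong there.

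The cost is one line in each place and two extra degrees of freedom in the primary model, out of roughly 240 evaluable subjects (300 less 20%). No new data, visits or subjects are needed. Fixing these terms in advance also limits later choice of covariates in an open-label trial.
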